### Statistical analysis

2.6

All statistical analyses will be performed using IBM SPSS Statistics version 29.0 (IBM Corporation, Armonk, NY, USA), with a significance level set at 5% (*p* < 0.05). Descriptive statistics (mean, standard deviation, 95% confidence intervals, and range) will be calculated for all outcome variables, including EEG spectral powers, oculomotor parameters, motor performance scores, and subjective fatigue ratings. These data will be stratified by group (experimental and control) and time (pre- and post-intervention) and presented visually using box plots and line graphs to facilitate interpretation (88, 89).

To assess the effect of mental fatigue, paired t-tests will compare pre- and post-intervention results within each group, while independent t-tests will compare the experimental and control groups at each time point (88, 90). For EEG outcomes, repeated-measures ANOVA models will include Time (pre vs. post mental fatigue) and Recording Condition (eyes open, eyes closed, motor imagery) as within-subject factors, and Group (experimental vs. control) as a between-subject factor (88, 90). Assumptions of normality and sphericity will be evaluated prior to analysis, following established recommendations for repeated measures designs (88, 91). When sphericity is violated, the Greenhouse-Geisser correction will be applied. Effect sizes will be reported using eta squared (*η*^2^), interpreted according to Marôco (90) as small (<0.04), moderate (0.04–0.25), or large (≥0.25). Statistical power (π) will also be reported when applicable (92, 93).

For EEG data (theta, alpha, and beta bands), spectral power within predefined regions of interest (ROIs) will be analyzed using repeated-measures models including Time (pre vs. post mental fatigue) and Recording Condition (eyes open, eyes closed, motor imagery), allowing evaluation of fatigue-related changes across neural states. Primary analyses will focus on frontal midline and posterior ROIs, consistent with the study's theoretical hypotheses. Exploratory analyses across additional scalp regions will be conducted separately and corrected using False Discovery Rate (FDR) procedures to control for multiple comparisons. Correlational analyses (Pearson's r) will explore associations between EEG bands and behavioral performance (LSPT, Y-SART), as well as subjective fatigue scores (VAS and FAS) (94, 95). Topographic maps will be generated to visualize EEG power distributions across cortical regions.

For oculomotor parameters (fixations, saccades, pupil diameter, blink rate), comparisons will assess the impact of mental fatigue on attention dynamics and visual search efficiency. Pearson correlations will explore links between ETS metrics, EEG patterns, and motor performance scores. Eye-tracking outcomes will be interpreted in conjunction with EEG measures, motor performance variables, and subjective fatigue scores, allowing a multimodal framework that reduces interpretative ambiguity.

Motor performance will be analyzed by comparing LSPT and Y-SART results before and after cognitive induction. Metrics such as execution time, technical penalties, and reaction times will be examined to determine whether cognitive fatigue impairs decision-making and technical execution under pressure.

These performance results will be correlated with neurophysiological and oculomotor indicators to investigate predictive relationships. Subjective fatigue will be analyzed using pre and post VAS comparisons and baseline FAS scores. These will be used to triangulate subjective perceptions with objective changes in EEG, ETS, and performance data. Higher self-reported fatigue scores are expected to align with reduced cortical efficiency, altered visual behavior, and degraded motor output.

To address individual variability, demographic and contextual variables (e.g., age, gender, field position, experience, sleep habits, caffeine intake) will be tested as covariates using ANCOVA or subgroup analyses. This will help determine whether certain profiles exhibit greater resilience or vulnerability to mental fatigue (10, 96).

Finally, multimodal integration will involve constructing correlation matrices and regression models to identify fatigue profiles across domains. This will allow for the identification of converging patterns across the EEG, ETS, motor, and subjective domains, thereby increasing the understanding of the neurocognitive and behavioral effects of mental fatigue. This approach is supported by advanced multivariate methodologies in sports neuroscience and applied psychology (39, 40).

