### Sample

2.2

Sample size was calculated using G*Power 3.1.9.7 software (41), considering a repeated measures ANOVA design with two groups (experimental *vs.* control) factors, and two measurement times (pre *vs.* post). The estimated minimum sample size at alpha 0.05 and statistical power of 80%, for moderate effect size (f = 0.25), was approximately 34 subjects (17 per group). At baseline, participants will be pre-screened using an online questionnaire to determine eligibility.

The inclusion criteria were: (i) minimum age of 18; (ii) at least one year of competitive football experience; (iii) no eye problems that impair vision; (iv) no history of neurological injuries; (v) abstinence of caffeine, alcohol and intense physical activities in the previous 24 h before each experimental session; (vi) having slept for at least 7 h the night before. On the other hand, the exclusion criteria were: history of neurological injury; uncorrected vision problems; diagnosis of psychological disorders; use of psychoactive substances in the last 24 h before the experimental sessions; any form of nystagmus for electrophysiological contraindications for electrophysiological recording. The operationalization and description criteria are summarized in Table 1.

**Table 1 T1:** Sample operationalization and description criteria.

Topic	Description	Operationalization
Age	Minimum age of 18 years	Participants aged 18 years or older. There is no maximum age limit stipulated in the protocol.
Gender	Gender balance	Sample of 24 men and 24 women, in equal number for experimental and control groups.
Competitive experience	Minimum of 1 year of competitive experience	Football players with a minimum of 1 year of regular practice in competitive condition
Health condition	No conditions preventing the practice of sport	Individuals with a history of neurological injuries, uncorrected visual problems, diagnosed psychological disorders, use of psychoactive substances in the last 24 h, or any clinical limitation to physical exertion will be excluded. Pregnant women will also be excluded.
Legal and ethical criteria	Compliance with current regulations	The study complies with the GDPR and the provisions of Decree-Law No. 5/2007, ensuring that all participants meet the legal and ethical conditions for physical exercise.

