#### Technical and motor performance

2.5.3

Technical and motor performance will be assessed using the LSPT and the Y-SART, using Witty SEM indicators (Microgate, Bolzano, Italy). These instruments allow the effects of mental fatigue on technical execution, reactive agility and decision-making processes in a sporting context to be quantified with high temporal precision and reliability.

Comparisons between groups will examine whether the ST induces greater impairments in performance metrics compared to a cognitively neutral task. The LSPT will provide data on total execution time, technical penalties, and adjusted score, while the Y-SART will produce reaction and execution times in response to visual stimuli. These comparisons will elucidate the degree to which mental fatigue affects motor fluency, visuomotor coordination, and accuracy under pressure.

Intra-subject analyses in the experimental group will allow for the detection of performance deterioration caused by the ST. By comparing pre- and post-intervention scores on both the LSPT and Y-SART, this approach will help determine whether mental fatigue results in statistically significant reductions in motor and technical efficiency.

The associations between performance metrics and indicators of fatigue (e.g., VAS, EEG, and ETS) will also be examined to explore whether higher levels of perceived or physiological fatigue correlate with slower and less accurate performance. These relationships may help identify which dimensions of fatigue are most predictive of declines in physical performance.

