The statistical approach defined in this methodology and experimental protocol is structured to support the analysis of neurophysiological, visual, motor, and subjective outcomes using established quantitative methods. Descriptive statistics will characterize each variable, while paired and independent t-tests will assess intra- and intergroup differences before and after the intervention. A repeated measures ANOVA will be used to examine the effects of time and group interaction, with assumptions of normality and sphericity tested to ensure validity. Effect sizes (*η*^2^) and test power (π) will be reported to improve the interpretability and generalization of the results, following Marôco (90), Pallant (89), and Field (88). Pearson's correlation will be used to explore associations between domains (e.g., EEG activity and motor performance), interpreted according to Marôco (90). When appropriate, ANCOVA will control for individual variability, such as age or training experience. This analytical framework supports the protocol's goal of detecting the effects of mental fatigue on various dimensions of performance, based on robust methodological and statistical criteria.

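### Section 2.6 lets the Stroop arm's own pre-post change count as the fatigue effect on LSPT, Y-SART, VAS and eye-tracking, and assigns these outcomes no between-group test of change

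*Protocol article*

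**What the plan says.** Section 2.6 (Statistical analysis) introduces the tests of the fatigue effect for all outcomes together: "paired t-tests will compare pre- and post-intervention results within each group, while independent t-tests will compare the experimental and control groups" at each time point. The next sentence gives a repeated-measures ANOVA with Time, Recording Condition and Group, but for EEG outcomes only. For the rest, section 2.6 describes LSPT and Y-SART as a comparison before and after induction, VAS as a pre-post comparison, and eye-tracking as comparisons of no stated form. The ANCOVA later in that section is for demographic and contextual covariates, not for the baseline value of the outcome.

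Three outcome sections attach a causal reading to the within-arm change:

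- Section 2.5.3 says that intra-subject analysis of the experimental group detects deterioration caused by the Stroop Task, and adds: "By comparing pre- and post-intervention scores on both the LSPT and Y-SART, this approach will help determine whether mental fatigue results" in poorer motor and technical efficiency.
- Section 2.5.2 takes the experimental group's pre-post oculomotor change as the direct impact of cognitive overload.
- Section 2.5.4.2 takes the experimental group's VAS change as the immediate impact of the intervention.

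Two other places point to a different test. Section 2.2 sized the trial "considering a repeated measures ANOVA design with two groups" and two measurement times. The Discussion says: "A repeated measures ANOVA will be used to examine the effects of time and group interaction". It names no outcome.

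**The concern.** The hypothesis at the end of the Introduction is comparative: the Stroop Task against a low-load control condition. Participants are randomised so that whatever happens to everyone during the session cancels out. A paired t-test in the experimental arm does not use the control arm, so anything that moves both arms enters its result.

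The schedule gives reasons to expect such movement. Both arms repeat the LSPT and Y-SART within one session, with 30 minutes between. Section 2.3 places the first VAS in Phase 2, before the first round of motor tests, and section 2.4 places the second after that round and the 30-minute task. Practice, exertion and elapsed time are therefore common to both arms. A shared deterioration could be reported as fatigue, and a shared practice gain could hide real fatigue.

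The planned between-group comparison at the post time point does not have this fault, but it discards the baseline that the trial collects. The plan does not say which result governs if the paired and independent tests disagree.

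**Working it through.** **Inputs from the protocol.** Section 2.2: two groups, two times, f = 0.25, alpha 0.05, power 80%, 34 participants (17 per group). Section 2.6: significance level 5%.

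**Assumptions.** The pre-post correlation r and the size of any change common to both arms are not stated. I use r = 0.5, 0.7 and 0.8, and shared shifts of 0.2, 0.3 and 0.5 SD. Outcomes are taken as normal with equal SD at both times, and tests are two-sided.

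**1. Reproduce the sample size.** For the Group x Time interaction with m = 2 times, λ = f²·N·m/(1 − r). At N = 34 and r = 0.5, λ = 0.0625 × 34 × 2 / 0.5 = 8.5. With 1 and 32 degrees of freedom the power is 80.7%, so 34 reproduces. The test of the between-group main effect would need 98. The stated number therefore fits a test that involves change over time, and it fits the interaction at r = 0.5. An interaction of f = 0.25 corresponds to a between-group difference in change of 4 × 0.25 = 1.0 SD.

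**2. Experimental-arm paired t-test when there is no fatigue effect.** A change score has SD √(2(1 − r)). For a shared shift d, the noncentrality is d·√17 / √(2(1 − r)) on 16 degrees of freedom. For example, d = 0.5 and r = 0.5 gives 0.5 × 4.123 / 1 = 2.06.

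| Shared shift | r = 0.5 | r = 0.7 | r = 0.8 |
|---|---|---|---|
| 0.2 SD | 12% | 17% | 23% |
| 0.3 SD | 21% | 32% | 45% |
| 0.5 SD | 49% | 71% | 86% |

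Simulation (40,000 trials per setting) agrees at the settings run: r = 0.5 and 0.7, shifts 0.3 and 0.5 SD.

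**3. Significant in the experimental arm but not in control.** The arms are independent, so with p from the table the probability is p(1 − p). At 0.5 SD this is 25% (r = 0.5), 21% (r = 0.7) and 12% (r = 0.8). Setting the two paired results side by side does not restore the 5% level.

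**4. The between-group tests under the same conditions.** In the simulation, with shifts of 0, 0.3 and 0.5 SD and r = 0.5 or 0.7, the post-intervention independent t-test and the Group x Time test both reject in about 5% of trials. If either the paired test or the post-intervention test is accepted as evidence, the rate is about 10% with no shared shift, 25% to 36% at 0.3 SD and 52% to 72% at 0.5 SD.

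**5. Power for a true 1.0 SD group difference, 17 per arm.** The residual variance is 1 for the post-only t-test, 2(1 − r) for change, and 1 − r² for ANCOVA. The noncentrality is the difference divided by √(variance × 2/17).

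| Test | r = 0.5 | r = 0.7 |
|---|---|---|
| Post-only t-test | 81% | 81% |
| Group x Time | 81% | 95% |
| ANCOVA on the pre value | 90% | 98% |

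For a 0.5 SD difference, the post-only t-test has 29% and ANCOVA 37% (r = 0.5) or 51% (r = 0.7).

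**The case against.** The strongest reply is that a valid between-group comparison is already planned for these outcomes. Section 2.6 includes an independent t-test at each time point, section 2.5.3 asks whether the Stroop Task impairs performance more than a neutral task does, and section 2.5.2 plans the same contrast for eye-tracking. This stands. The post-intervention t-test is a proper randomised comparison. A reader might infer that it too is inflated by shared change; it is not. At r = 0.5 it also has the same power as the interaction on which the trial was sized, and its loss against ANCOVA is one of efficiency, not validity. But the plan sets beside it a paired test with explicit causal wording, and no rule says which decides.

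A reader might also infer that no Group x Time test is intended outside EEG. The documents do not support that: the Discussion plans a time-and-group interaction ANOVA without limiting it to any outcome, and section 2.2 sizes the trial on such a design. The supported reading is that section 2.6 conflicts with those sections.

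Nor is Group missing from the EEG model. Section 2.6 later describes EEG as analysed "using repeated-measures models including Time (pre vs. post mental fatigue) and Recording Condition", without Group, but the preceding paragraph names Group as the between-subject factor. The later sentence is an abbreviation.

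Finally, the rates depend on an assumed shared shift. The range is shown for that reason; even 0.2 SD more than doubles the nominal 5%. Softer phrasing in section 2.5.3, that the comparison will help determine the effect, does not cancel the statement in the same paragraph that the deterioration is caused by the task.

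**Conclusion.** The concern holds for the within-arm paired tests and for the causal reading of the experimental arm's change. If both arms share a shift of 0.2 to 0.5 SD and there is no fatigue effect, the experimental-arm test would be significant in about 12% to 49% of trials at r = 0.5 and 23% to 86% at r = 0.8. These figures rest on the assumed shifts and correlations and on normality. With no shared change, the paired test keeps its 5% level.

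The post-intervention independent t-test is valid but gives up precision: 81% power against about 90% to 98% for ANCOVA at a 1.0 SD difference, with r from 0.5 to 0.7. Sections 2.2, 2.6 and the Discussion disagree on whether a group-by-time test applies to the non-EEG outcomes and must be reconciled before data are analysed.

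**What to change.** - In section 2.6, name one between-group test of the fatigue effect for each LSPT, Y-SART, VAS and eye-tracking outcome. The preferred test is an ANCOVA of the post value on Group, adjusted for the pre value of the same outcome. The Group x Time interaction on which the trial was sized is an acceptable alternative. Report the group difference with its 95% confidence interval.
- For EEG, state that the Group x Time term is the test of fatigue.
- Report within-arm pre-post changes as description only, and remove the causal wording about experimental-arm change from sections 2.5.2, 2.5.3 and 2.5.4.2.
- Align section 2.6 with section 2.2 and the Discussion.
- Confirm that eye-tracking is recorded at the pre-test LSPT. Section 2.4 mentions continuous recording when describing the repeated tests, which leaves the first round unclear, although section 2.5.2 relies on a pre-post comparison. Baseline adjustment needs that recording.

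The cost is wording. Under the plan's own inputs with r = 0.5, the interaction has 80.7% power at 34 participants and ANCOVA about 90%, so no larger sample is needed. No new data are required if the pre-test eye-tracking recording is confirmed.

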## Abstract

Mental fatigue, induced by prolonged cognitive demands, impairs attention, decision-making, and motor coordination, potentially compromising performance in cognitively demanding sports such as football. This study presents a randomised controlled experimental design pre-test/post-test protocol designed to investigate the effects of mental fatigue on neurophysiological, visual, technical, and motor performance in football players. Thirty-four athletes (17 men, 17 women; aged ≥18 years; ≥1-year competitive experience) will be randomly assigned to either a cognitive fatigue induction group (30 min Stroop Task) or a low cognitive load control group. Data collection will include EEG (theta and alpha bands), eye tracking (fixation, saccades, pupil dynamics), sport-specific tasks (Loughborough Soccer Passing Test, Y-Shaped Agility Reaction Test), and subjective fatigue ratings (Fatigue Assessment Scale; Visual Analogue Scale). Statistical analyses will encompass intra- and inter-group comparisons, correlation and regression models. By integrating subjective, physiological, and performance indicators in a sport-specific, ecologically valid design, this protocol aims to deepen understanding of how mental fatigue affects performance and to inform individualized monitoring and intervention strategies in high-performance contexts. As a protocol paper, no data are yet available. However, based on previous literature, mental fatigue is expected to be associated with changes in EEG oscillatory activity, less efficient gaze behaviour, and impaired football-specific performance compared to the control condition.

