Following baseline assessment, all participants will be randomly assigned to either the experimental group or the control group (Phase 4). The experimental group will perform a cognitively demanding task, the ST, for 30 min, designed to induce mental fatigue through sustained attention and inhibitory control demands. Although the ST does not reproduce the full cognitive complexity of real football match situations, it is widely used in experimental research to induce a controlled state of mental fatigue under standardized conditions (4, 8). In the present protocol, it is not intended to simulate football-specific decision-making demands, but rather to induce mental fatigue prior to sport-specific performance assessment. This separation between fatigue induction and performance testing allows clearer interpretation of the neurophysiological and behavioral consequences of mental fatigue. In contrast, the control group will engage in a low-demand relaxation condition, consisting of reading neutral magazines for the same duration (30 min), thereby maintaining minimal cognitive load while controlling for time-on-task effects.

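### The plan balances the arms by sex, but the between-arm t-tests have no sex term, so they are conservative and lose power if sex is prognostic and the balance is achieved

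*Protocol article*

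**What the plan says.** Table 1 in section 2.2 of the Protocol article sets the composition of the arms: "Sample of 24 men and 24 women, in equal number for experimental and control groups". That implies 12 men and 12 women per arm. The Abstract gives a different total: "Thirty-four athletes (17 men, 17 women; aged ≥18 years; ≥1-year competitive experience) will be randomly assigned". On allocation, section 2.2 says only that "all participants will be randomly assigned to either the experimental group or the control group (Phase 4"), and it describes no stratification by sex.

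For the analysis, section 2.6 assesses the fatigue effect by paired t-tests within each group, while "independent t-tests will compare the experimental and control groups at each time point". A repeated-measures ANOVA is specified there for EEG. The Discussion mentions an ANOVA for time and group in general terms. Neither has a sex term.

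Gender appears later in section 2.6, in a list of demographic and contextual variables that "will be tested as covariates using ANCOVA or subgroup analyses", with the aim of finding profiles that resist or suffer from fatigue. Sections 2.2 and 2.5.5 call these covariates exploratory, and section 2.2 places them in secondary analyses.

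**The concern.** When a prognostic factor is balanced between arms, it drops out of the true variance of the arm difference. A two-sample t-test on pooled men and women does not know this. It estimates the error variance within each arm, and that variance still contains the gap between the sexes. The standard error is then too large, the confidence interval too wide and the p-value too high.

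The outcomes concerned are those for which section 2.6 specifies no fuller model: LSPT, Y-SART, VAS and gaze. Men and women may well differ on execution and agility times, so the planned comparison could miss a real effect that the same data would show with sex in the model. The trial is small and has little power to spare.

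**Working it through.** **Inputs.** Alpha 0.05 (section 2.6), taken as two-sided. Arms of 24 with 12 men and 12 women (Table 1), or arms of 17 (section 2.2 and Abstract). The sex difference g is in within-sex SDs and is assumed, because the article gives none.

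**1. The plan's own figure.** The sample size was obtained "considering a repeated measures ANOVA design with two groups" and two times. The minimum "at alpha 0.05 and statistical power of 80%, for moderate effect size (f = 0.25), was approximately 34 subjects (17 per group"). For the Time × Group interaction, λ = f²·N·m/(1−ρ). With f = 0.25, N = 34, m = 2 and an assumed ρ = 0.5, λ = 0.0625 × 34 × 2 / 0.5 = 8.5 on 1 and 32 df, and power is 0.807. The figure of 34 reproduces. It depends on ρ: 0.3 would give 46 and 0.7 would give 22. The 80% therefore belongs to this ANOVA. An independent t-test at one time point with 17 per arm has about 29% power at d = 0.5 (taken as the equivalent of f = 0.25) even if sex plays no role.

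**2. Why the t-test is conservative under balance.** With 12 + 12 per arm and unit within-sex variance, sex adds g² × 12 × 12 / 24 = 6g² to the sum of squares in each arm, on 23 df. The expected pooled variance is 1 + 6g²/23, while the variance that governs the arm difference is 1.
- g = 0.5: 1 + 1.5/23 = 1.065, so the SE is too large by √1.065 = 1.032. The effective critical value is 2.013 × 1.032 = 2.078, a two-sided tail of about 4.3%.
- g = 1.0: 1 + 6/23 = 1.261, √1.261 = 1.123, and 2.013 × 1.123 = 2.260, a tail of about 2.9%.

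**3. Simulation, 24 per arm (12/12), 100,000 runs per cell.**

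| g | Type I, t-test | Type I, with sex | Power at d = 0.5, t-test | Power at d = 0.5, with sex |
|---|---|---|---|---|
| 0 | 5.0% | 5.0% | 39.7% | 39.7% |
| 0.5 | 4.4% | 5.0% | 37.3% | 39.7% |
| 0.8 | 3.5% | 5.0% | 33.6% | 39.4% |
| 1.0 | 2.9% | 4.9% | 30.6% | 39.5% |
| 1.5 | 1.5% | 5.0% | 22.0% | 39.4% |

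The loss at d = 0.5 is 39.7 − 37.3 = 2.4 points at g = 0.5 and 39.5 − 30.6 = 8.9 points at g = 1.0.

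**4. 17 per arm.** Seventeen men cannot be halved, so the closest split is 9/8 and 8/9. The unadjusted arm difference then carries a shift of (9 − 8)/17 × g = 0.059g. The type I error is 4.4% at g = 0.5 and 3.1% at g = 1.0. Power at d = 0.5, against 29% with sex in the model, depends on the direction of the extra man:
- With the effect: 30% (g = 0.5) and 27% (g = 1.0).
- Against the effect: 24% and 17%.

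**5. Simple randomisation, 17 men and 17 women.** The type I error is 4.8% at g = 1 and 5.0% at g = 2. Power at d = 0.5 falls from 29% (g = 0) to 24% (g = 1) and 17% (g = 2). Only power is lost.

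**6. What is not affected.** If men and women differ by the same amount before and after, that amount cancels in post minus pre. The paired t-tests and the Time × Group term of the ANOVA therefore do not carry it.

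**7. Use of the pre-test.** For the post value with 24 per arm, g = 1.0, effect 0.8 SD and assumed within-sex ρ = 0.5, power is:
- unadjusted t-test 70%
- sex only 78%
- change score 77%
- pre value as covariate 86%
- pre value and sex 87%

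**The case against.** **Covariate control is foreseen.** Section 2.2 says the questionnaire data will serve to control confounding, and the Discussion allows ANCOVA where appropriate. Gender is on the ANCOVA list in section 2.6, and an analysis plan not shown might settle the rest. This stands in part: it would be wrong to say that the plan ignores sex. But the article itself names the between-arm test, and that test has no covariate.

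**The 80% power.** A reader might infer that the pooled t-test erodes the stated 80%. The documents do not support that. The 80% was computed for a repeated-measures ANOVA, in which a constant sex difference cancels from Time × Group. The Discussion may even intend that ANOVA for all outcomes, although section 2.6 specifies it only for EEG.

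**The premise is conditional.** A reader might also infer that the p-values and intervals are simply wrong. That would need a known sex effect and forced balance. The article gives no sex difference for any outcome, VAS and gaze included, and describes no stratified allocation. With g = 0 nothing is lost, and under simple randomisation the test keeps its level. This objection stands, and it limits the point to a conditional one.

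**Baseline matters more.** In step 7, adding the pre value recovers more power than adding sex. At 24 per arm, sex then adds only 0 to 3 points. This stands and shapes the fix.

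**The error is conservative.** It does not inflate false positives. That is correct and limits the severity.

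**Conclusion.** The point holds in conditional form. The plan promises sex balance by arm, and its stated between-arm t-tests do not use it. If the balance is achieved and sex is prognostic, those tests are conservative and lose power. With 24 per arm and assumed sex differences of 0.5 to 1.0 within-sex SD, true alpha is about 4.4% to 2.9%, and the loss at d = 0.5 is about 2 to 9 points. If allocation is simple randomisation, alpha stays near 5% and the harm is lost power alone. With 17 per arm, the unadjusted estimate also carries a one-man imbalance.

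The result rests on the assumed sex differences, normal outcomes and two-sided tests. It concerns only the between-arm t-tests on LSPT, Y-SART, VAS and gaze outcomes. It is a cheap improvement that should be made, and it does not threaten the validity of the trial.

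**What to change.** In section 2.6, replace the unadjusted between-arm t-test for LSPT, Y-SART, VAS and gaze outcomes with a linear model containing Group and sex. Preferably fit it to the post value with the pre value as a further covariate, and report the adjusted arm difference with its 95% CI. Section 2.4 leaves it unclear whether gaze is recorded at the pre-test, while section 2.5.2 plans a pre-post comparison. If no pre value exists for gaze, that model keeps Group and sex only.

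In section 2.2, state whether randomisation is stratified by sex, and reconcile the 48 of Table 1 with the 34 of the Abstract and the sample-size text, since 17 men cannot be divided equally. Keep the search for resilient and vulnerable profiles in section 2.6 separate and exploratory.

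The cost is a few sentences and one degree of freedom for sex, or two with the pre value. Gender is already collected, and no participants or procedures are added.

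### The primary EEG test uses the pre-randomisation EEG as a level of Time instead of as a covariate; it is valid but less efficient, by about 9 points of power if the unstated pre-post correlation is 0.5

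*Protocol article*

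**What the plan says.** Section 2.3 places the first EEG recording in Phase 2. Section 2.2 places allocation later: "Following baseline assessment, all participants will be randomly assigned to either the experimental group or the control group (Phase 4"). Section 2.4 puts the second EEG at the end of Phase 5.

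Section 2.5.1.1 designates the analyses of the predefined regions of interest in the theta, alpha and beta bands as primary, and section 2.6 repeats this: "Primary analyses will focus on frontal midline and posterior ROIs, consistent with the study's theoretical hypotheses". The model for them is given in section 2.6: "repeated-measures ANOVA models will include Time (pre vs. post mental fatigue) and Recording Condition (eyes open, eyes closed, motor imagery) as within-subject factors", with Group as the between-subject factor. The Discussion names the interaction of time and group as what this ANOVA examines.

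ANCOVA appears in section 2.6 and in the Discussion only for demographic and contextual variables such as age, gender or training experience. The baseline value of the EEG outcome is not named as a covariate anywhere.

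The sample size in section 2.2 rests on a repeated-measures ANOVA with two groups and two times: "The estimated minimum sample size at alpha 0.05 and statistical power of 80%, for moderate effect size (f = 0.25), was approximately 34 subjects". No pre-post correlation is stated.

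**The concern.** A measurement taken before randomisation cannot be affected by the allocated task. It is most useful as a predictor of the later value. Treating it as a second outcome, through the Time factor, fixes its weight at minus one, and the data are not allowed to set the weight. Unless pre and post values are very highly correlated, subtracting the whole baseline adds noise to the group comparison.

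The EEG question in section 2.5.1.2 is whether the Stroop group changes more than the control group. With about 17 participants per group, avoidable noise widens the interval for that comparison and raises the chance of missing a real effect, although the data that would remove the noise are already being collected.

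**Working it through.** **Inputs.** From section 2.2: N = 34 (17 per group), f = 0.25, alpha 0.05, two groups, two times. Not stated, so assumed and varied: the pre-post correlation rho. Also assumed: equal pre and post variances and no dropout. For the EEG model, the SD and rho refer to power averaged over the three recording conditions, and power is for one region and band at the 5% level.

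**Reproducing the plan's figure.** For the Group x Time interaction, lambda = f² x N x m / (1 - rho), with m = 2 times and df (1, N - 2). At rho = 0.5:
- lambda = 0.0625 x 34 x 2 / 0.5 = 8.5, df (1, 32), power 80.7%.
- N = 32 gives 78.1%, so the minimum even N is 34, as stated.
- Other correlations give other sizes: 46 at rho 0.3, 28 at 0.6, 22 at 0.7.

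So rho = 0.5 is the value that fits; 0.46 to 0.55 keeps N within 2 of 34.

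**Effect size.** In a 2 x 2 interaction the four cell effects are plus or minus D/4, where D is the between-group difference in change. Hence f = D/4, and f = 0.25 means D = 1.0 SD.

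**Precision of the two analyses.** In units of the outcome variance:
- Change score, which is the Group x Time test: 2(1 - rho).
- Post value adjusted for baseline: 1 - rho².
- Ratio: (1 + rho)/2, below 1 for any rho below 1. At rho 0.5 it is 0.75.

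At rho 0.5 the change score has variance 2 x 0.5 = 1, the same as the post value alone. At the correlation that reproduces N = 34, the planned test therefore draws no power from the baseline EEG.

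**Power of the adjusted analysis at rho 0.5.** lambda = D² x N / (4(1 - rho²)) = 34 / (4 x 0.75) = 11.33, df (1, 31), power 90.3%. Allowing for chance baseline imbalance by dividing lambda by 1 + 1/(N - 4) = 1 + 1/30 gives 10.97 and 89.4%. A simulation of 200,000 trials gave 89.3%. The net gain is 89.4 - 80.7 = 8.7 points.

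**Dependence on rho, N = 34, imbalance allowed for.**

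| rho | D = 1.0 SD: planned / adjusted | Gain | Planned test held at 80.7%: adjusted | Gain |
|---|---|---|---|---|
| 0.3 | 66.6% / 83.0% | 16.3 | 93.1% | 12.4 |
| 0.5 | 80.7% / 89.4% | 8.7 | 89.4% | 8.7 |
| 0.6 | 88.5% / 93.5% | 5.0 | 87.4% | 6.7 |
| 0.7 | 95.4% / 97.3% | 1.9 | 85.4% | 4.7 |
| 0.8 | 99.4% / 99.6% | 0.2 | 83.4% | 2.7 |
| 0.9 | 100.0% / 100.0% | 0.0 | 81.3% | 0.6 |

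(Gains are taken from unrounded values.) Over rho 0.46 to 0.55 with D = 1.0 SD, the gain runs from 10.2 down to 6.8 points.

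**If Table 1's 24 men and 24 women are the sample.** At N = 48, rho 0.5 and D = 1.0 SD, the planned test has 92.4% and the adjusted one 97.2%, a gain of about 5 points.

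**The case against.** The strongest reply is that nothing here is wrong. Under randomisation the Group x Time test is valid and unbiased. The sample size and the EEG analysis come from the same family of model, and at the inputs that reproduce 34 participants the test delivers the promised 80%. EEG is also the one domain for which section 2.6 explicitly puts Group and Time into a single model. All of this stands, and it makes the point one of efficiency.

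A second reply is that the gain rests on a correlation the article never gives. This also stands. A reader might infer that the plan's own inputs imply a loss of about ten points. They do not: rho is back-solved from N, the calculation in section 2.2 is for a generic two-by-two design not tied to EEG, and the relevant correlation is that of condition-averaged EEG power within one session. If it is 0.7 or higher, the gain is under 5 points.

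A reader might also take the Group main effect of the ANOVA as the test of the EEG hypothesis and object that it averages in a value from before the intervention. The Discussion names the time and group interaction as the target, so that objection does not apply.

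A third reply is that the ANOVA is needed to see whether effects differ between eyes open, eyes closed and motor imagery, as section 2.3 intends. That is a reason to keep Recording Condition in the model. It is no reason to keep the baseline as a level of Time.

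**Conclusion.** The point holds as lost efficiency in an analysis designated primary. It is not an invalid test, and the stated power is not wrong. If rho is 0.5 and the difference is 1.0 SD, baseline adjustment raises power from 80.7% to about 89% at 34 participants. At the same planned power, the gain is about 12 points at rho 0.3 and 3 at rho 0.8, and it nearly vanishes at 0.9. The figures assume equal pre and post variances, complete data, and a test averaged over recording conditions. The direction of the gain does not hinge on the exact correlation: it is positive, if at times negligible, across the range examined (0.3 to 0.9). The article gives no reason for preferring the less precise analysis.

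**What to change.** In section 2.6, for each primary region and band, make the primary test the Group effect in a mixed model (SPSS MIXED) of post-intervention power. Include Group, Recording Condition and Group x Condition, with participant as the repeated unit. Use baseline power in the same region, band and recording condition as covariate, with Condition x baseline so that the slope may differ between conditions. The covariate must be named this precisely, because each participant has three baseline recordings, and a condition-matched covariate calls for MIXED because repeated-measures GLM takes only participant-level covariates.

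A simpler version for the overall Group question is ANCOVA of the condition-averaged post value on the condition-averaged baseline; the power figures above are for this version. Keep the Time x Condition x Group ANOVA as supportive. Stating the assumed pre-post correlation in section 2.2 would let readers judge the gain.

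The cost is a few sentences, one degree of freedom for the averaged version or a few for the mixed model, and a small penalty for chance baseline imbalance, already counted above. It needs no new data, participants or software.
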